**Table 1 Tab1:**
[figure not shown]
Schedule of enrolment, interventions, and assessments

### Participants, interventions, and outcomes

#### Ethical approval

The multicentric RCT is conducted in agreement with the principles of the Declaration of Helsinki and the guidelines of Good Clinical Practice. Written informed consent will be obtained from all participants or their legal guardians before enrolment in the study. The local ethics committee of the TU Berlin, Germany has approved the study protocol *(No GR_14_20191217).* The trial was registered at DRKS.de with registration number DRKS00021423 on April 16, 2020.

#### Recruitment of participants

To assure eligibility and recruitment of participants, staff consultation and nursing documentation will be applied primarily. To gain a sufficient number of participants, the institutions involved are deliberately selected based on their number of nursing places (> 100).

##### Eligibility criteria

Inclusion criteria are *i)* willingness to participate, *ii)* ability to participate in group activities, *iii)* ability to walk (with or without walking aid), and *iv)* the ability to understand and execute simple instructions including visual presentations of landmarks. No other inclusion or exclusion criteria will be applied.

#### Assignment of interventions

To avoid selection bias, stratified randomization will be conducted to divide participants into an intervention group and a wait-list control group. The random allocation will be stratified according to sex, age, and cognitive performance to avoid differences in the baseline conditions between the groups. Data collection will be done by blinded assessors; data will be stored securely and in pseudonymized form using a coded ID number to maintain participants’ confidentiality. To avoid performance bias, the measurements and the interventions follow a standardized protocol.

### Outcome measures

The assessment will focus on three key domains: physical functioning (especially LS mobility), cognitive performance (especially spatial orientation), and psychosocial well-being. Apart from the following primary and secondary outcomes, demographic and baseline characteristics, such as chronological age, body height, body mass, body mass index, and sex will be assessed.

#### Primary outcomes

The following primary outcomes will be measured to evaluate the efficacy of the intervention programs (see Fig. 1):

**Fig. 1 Fig1:**
[figure not shown]
Schematic description of the study design, the outcome measures, and the intervention characteristics

##### Mobility

The smartphone-based instrument Timed Up and Go Test (iTUG) is a reliable measure of mobility [67]. The instrumented TUG takes 5–10 min. The test includes two repetitions of the same task, the participants are asked to rise in a comfortable and safe pace from a chair, walk three meters, turn around, walk back to the chair and sit down.

##### Physical activity

The “activPAL4™ micro” accelerometers (PAL Technologies Ltd., Glasgow, Scotland) will be worn to assess participants’ PA for a full 7 days. The main outcomes are the number of steps as well as the proportion of PA and sedentariness per day. The reliability was judged as good to excellent (inter-device reliability range = 0.79 to 0.99) and it is a valid measure for posture and motion during everyday PA [68].

##### Life-space mobility

The Nursing Home Life-Space Diameter (NHLSD) represents an external measure of LS mobility among nursing home residents [69]. This proxy-assessment will be administered to nursing staff and can be used to monitor changes or the effect of interventions on LS mobility [69]. The interrater (Pearson’s r = 0.951) and the intrarater (Pearson’s r = 0.922) reliability of the NHLSD is excellent [69]. The extent of LS mobility is measured by dividing the nursing home into four zones: (1) the resident’s private room, (2) the ward on which she/he resides, (3) the rest of the facility beyond the ward, (4) and the area outside of the facility [69]. Frequency of travels to each of the four zones is grouped into 0 = never, 1 = less than weekly, 2 = at least weekly, 3 = > 2 times a week, 4 = 1–3 times a day, and 5 = > 3 times a day; this score is then multiplied with 1 to 4 (congruent with the value of the zones, 1 to 4) and summed up. Independence of movement can be incorporated into the overall score by multiplying it with two in case of travel without human assistance.

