**Methods:**

A three-arm single-blinded multicenter RCT with a wait-list control group will be conducted in a sample of 513 individuals (needed according to power analysis) in three different regions in Germany. In each nursing home, one of three different intervention approaches will be delivered to participating residents for 12 weeks, twice a week for 45 min each: The *PROfit basic* group will perform functional strength, balance, flexibility, and walking exercises always at the same location, whereas the *PROfit plus* group changes the location three times while performing similar/the same exercises as the PROfit basic group. The *PROfit orientation* group receives navigation tasks in addition to the relocation during the intervention. Physical and cognitive functioning as well as psychological measures will be assessed in all study groups at baseline. Participants will then be randomized into either the intervention group or the wait-list control group. After 12 weeks, and after 24 weeks the measures will be repeated.

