### Trial design

Based on the existing research and the physical training recommendations mentioned above, a multicenter intervention study will be conducted, aiming to determine the feasibility and efficacy of three different exercise intervention programs for residents of nursing homes. The type of intervention program will be randomly assigned to the participating nursing homes. The participants’ allocation to the intervention or wait-list control group will be randomized after baseline assessment in each nursing home. The assessment of primary and secondary outcomes will take place upon entry to the study (T1) by a blinded assessor and will be repeated at twelve (T2) and at 24 weeks (T3) (see Table 1).

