*PROfit basic* focusses on daily situations which are commonly associated with increased fall risk. It mainly consists of challenging walking exercises (e.g. brisk walking, starting, stopping, avoiding obstacles, turns). During these exercises, participants are also exposed to a variety of cognitive tasks under dual-task conditions designed to tax specific executive functions and to challenge their focus of attention using acoustic and visual stimuli. Furthermore, exercises for strength, balance, and flexibility as well as endurance performance associated with walking are integrated (cf. Table 2).

There is a focus on everyday skills to promote ADL, cognition and psychosocial resources considering residents’ desires and preferences. For example, by using motivational equipment with different colors during the exercise sessions, a stimulating environment will be provided.
(2)*PROfit plus*

The main structure and contents of the *PROfit basic* intervention will be transferred into the *“PROfit plus” intervention*. In contrast to the basic intervention, the participants will perform the walking exercises throughout the facilities and attend predefined spots in the nursing home. There will be four areas where the activities (1. warm-up/mobilization; 2. coordination and balance; 3. muscle strengthening exercises; 4. cool-down) will be conducted. The walking part of the program will be used to reach these areas. The trainer will check if all participants walk a progressing distance comparable to the *PROfit basic* intervention.
(3)*PROfit orientation*

The *PROfit orientation* intervention integrates navigation and orientation tasks into the walking route including tasks for egocentric and allocentric orientation. The training integrates pointing to specific predefined landmarks (allocentric and egocentric reference frame), remembering the order of landmarks encountered along the route (route knowledge), and navigating to a specific room or area in the facility (planning and navigation). Other navigation and orientation tasks are integrated into the warm-up/mobilization and the coordination, balance, and executive function parts of the training, e.g. pointing or moving to cardinal directions (direction pointing) or assembling sections of the facility map like a puzzle (cognitive map).

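### The primary life-space score (NHLSD) is reported by nursing staff who very probably know who trains, and as defined it counts trips made for the training itself

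*Protocol article*

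**What the plan says.** All references are to the protocol article.

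- **Status of the outcome.** Life-space mobility is listed under Primary outcomes, introduced by "The following primary outcomes will be measured to evaluate the efficacy of the intervention programs".
- **Source of the data.** The Life-space mobility section says of the NHLSD: "This proxy-assessment will be administered to nursing staff".
- **Scoring.** The same section groups "Frequency of travels to each of the four zones" into codes 0 to 5, multiplies each code by the zone number (1 to 4) and sums. Zone 3 is the facility beyond the resident's ward. No trips are excluded, and no rating period is given. Doubling for unassisted travel is optional.
- **Blinding.** The abstract describes "A three-arm single-blinded multicenter RCT with a wait-list control group". Assignment of interventions says "Data collection will be done by blinded assessors", without naming any outcome as an exception.
- **Randomisation.** The programme is assigned to the home. Under Trial design, allocation of residents to the intervention or "wait-list control group will be randomized after baseline assessment in each nursing home".
- **Delivery.** All three programmes run two sessions a week for twelve weeks, in groups of no more than 15. PROfit basic does its "walking exercises always at the same location". PROfit plus participants walk through the building and "attend predefined spots in the nursing home", and PROfit orientation has the same three location changes. The wait-list group carries on as usual for twelve weeks and then receives the home's programme.

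**The concern.** Two features of this primary outcome could produce a group difference that is not a change in spontaneous life-space.

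First, the information comes from staff of the home where trained and wait-list residents live side by side. Group sessions twice a week for twelve weeks are hard to miss. A blinded assessor who hands over the form does not blind the person who answers it. If staff expect the training to help, their frequency ratings may lean that way.

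Second, the quantity rated is how often a resident enters each zone. A trip to a training session is such an entry. The article's rationale (Discussion) is that better way-finding should carry over into everyday life-space, and attending a scheduled session is not evidence of that.

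Both features act at T2, when only the intervention groups have trained. The planned post-hoc tests compare baseline with this assessment. A significant NHLSD result could then partly reflect attendance and rater expectation, while the article tells the reader that data collection was blinded.

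**Working it through.** The article gives no figure for this effect, so there is none to reproduce. The check applies the article's own scoring rule to its own training schedule.

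**Inputs from the article**
- Codes: 0 never, 1 less than weekly, 2 at least weekly, 3 more than twice a week, 4 one to three times a day, 5 more than three times a day.
- Zone weights: 1, 2, 3, 4.
- Sessions: 2 a week in every programme.
- Location changes: 3 per session in PROfit plus and PROfit orientation, none in PROfit basic.

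**Assumptions not in the article**
- Sessions take place in zone 3.
- The rating period overlaps the training weeks.
- The resident attends both weekly sessions, and each session is rated as one trip.

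**Range of the score.** 5 × (1 + 2 + 3 + 4) = 50, without the optional doubling.

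**Gain from two session trips a week** = (code with sessions − code without) × 3.

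| Other zone-3 trips | Code without → with | Gain in points |
|---|---|---|
| None | 0 → 2 | (2 − 0) × 3 = 6 |
| Less than weekly | 1 → 2 | (2 − 1) × 3 = 3 |
| One or two a week | 2 → 3 | (3 − 2) × 3 = 3 |
| Three or four a week | 3 → 3 | 0 |
| Once or twice a day | 4 → 4 | 0 |

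Residents near the edge of a band can differ. With five other trips a week, two more make seven, or one a day: 3 → 4, a gain of 3. If a rater averages in the occasional trips of a less-than-weekly resident, the count passes two a week: 1 → 3, a gain of 6.

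**Between programmes.** With one trip rated per session, the gain is the same in all three programmes if their sessions are all in zone 3, and it is 0 in the wait-list group at T2. A gap between programmes needs each relocation to be rated as its own zone-3 trip. Plus and orientation then have 3 × 2 = 6 entries a week. For a resident with no other zone-3 trips that is code 3, a gain of 3 × 3 = 9, against 6 in basic. Plus and orientation tie, because Table 2 gives them the same location changes over the same distances.

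**Group level.** If a share p of a trained group otherwise never goes to zone 3 and the rest gain nothing, the mean shift is 6p points. The article gives neither p nor a standard deviation. For p from 25% to 100% the shift is 1.5 to 6 points. With an assumed standard deviation of 10 to 20 points, that is 1.5 / 20 = 0.075 to 6 / 10 = 0.6 standard deviations. The upper end is unlikely, since every participant must be able to walk and to join group activities.

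**At T3.** The wait-list group trains after week 12. If the T3 rating overlaps its sessions, the same gains go to the control group.

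**With session trips excluded,** the direct gain is 0 in every group by construction. The informants' knowledge of allocation remains.

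**The case against.** **An assessor can be blinded while an informant is not.** The self-reported primary outcomes work this way, and the trial claims only single blinding. This stands in part. The two passages do not flatly contradict each other, and that staff know the allocation is inferred, not stated. But an unqualified blinding statement will be read as covering a primary outcome that is rated by a third party, and for the content of the NHLSD it does not.

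**The rating period and rater instructions belong in a manual.** That is fair, and their absence from an article is no fault in itself. T2 comes at twelve weeks, so a session-free rating period is possible, and the artefact would then be zero. What remains is the definition the article does give: all travel counts, and two of the programmes consist partly of travel.

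**Many residents would gain nothing.** This stands. In general the gain is 0 for anyone already in zone 3 more than twice a week, and the session zone is not stated. Doubling the gains for independence is doubtful, because it is optional and session trips are led by a trainer. The doubled gains are not relied on here.

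**A stronger reading is tempting:** that the score is biased towards the full hypothesised order of wait-list, basic, plus, orientation. The article does not support it. Trip counting cannot separate orientation from plus, and it separates plus from basic only if relocations are rated one by one. Rater expectation might add to the order, but nothing in the article lets one size that.

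**Conclusion.** The point holds in a limited form. The blinding statement does not extend to the information in the NHLSD. This rests on the inference that staff of a home notice who attends its group sessions, which is strong given randomisation within homes. Separately, the score as written includes session trips. If the sessions are off the ward and the rating period overlaps them, this is worth 6 points out of 50 for a resident with no other zone-3 travel, 3 for an infrequent visitor, and generally 0 for one who already goes more than twice a week. If either condition fails, the zone-3 gain is zero.

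The direction is clear for trained against wait-list residents at T2, conditional for plus and orientation against basic, absent for orientation against plus, and possibly reversed at T3. It should not be read as showing that any NHLSD effect would be spurious. It shows that such an effect could not be cleanly separated from attendance and expectation. A cheap change to a primary outcome is warranted.

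**What to change.** 1. At T1, T2 and T3, and with the same wording for all groups, instruct raters not to count any trip to, from or during a PROfit session, and to rate a period in which the resident had no sessions.
2. Limit the blinding statement to the assessor-measured outcomes, say that the NHLSD informants are not blinded, and interpret NHLSD effects accordingly.

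The cost is one rater instruction, one corrected sentence and some care in timing the T2 and T3 ratings around the sessions. No extra raters are needed. The downside is a more modest claim for the NHLSD: the first change removes the counting artefact but does not blind the informants.

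The accelerometer outcome should not take the NHLSD's place. It records steps and sedentary time, not life-space, and if worn in training weeks it would also record session steps.

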##### Spatial orientation

The Perspective Taking Test is a reliable (Cronbach’s alpha = .82) and valid measure of spatial orientation [70]. It contains a sheet of paper with a consideration of seven objects, which is visible at all times. Each participant gets twelve task sheets with a circle on them. For each task the participants are asked to imagine being at the position of the object in the center of the circle, facing another object, and are asked to specify the direction to a third object [71]. The number of examples, the instructions, and the operation of the test is adapted to the target group of nursing home residents.

To assess landmark recognition, we will adapt the tasks conducted by Deipolyi and colleagues [72], which were already used with cognitively impaired older adults. In this test, participants have to identify which three landmarks out of a set of ten landmark pictures cannot be found in or around the facility. The pictures show landmarks that can be located in the participant’s own room, on the floor level of their own room, inside the facility or outside, close to the facility. Afterwards, the participants have to sort the pictures showing landmarks from their facility by distance, starting from their current position. As the last step, they position the landmarks on an overview map of the facility and surroundings.

Furthermore, a pointing task will be used to ask participants to point to their own room and to six other landmarks in or around the facility, which are also used for the landmark recognition task. Bryant [73] reports that pointing errors significantly correlate with self-ratings of sense of direction (r = − 0.63), worrying about becoming lost (r = 0.51), and mental rotation (r = − 0.39).

Besides, we will assess subjective navigation abilities by a modified 19-item self-report measure of environmental spatial strategies [74]. The questionnaire reflects three different aspects of spatial orientation in a five-point Likert scale, “1” representing “totally agree” and “5” representing “totally disagree”. Self-reported navigational abilities are associated with the use of strategies for finding the way [75]. Several studies identified significant relations between self-reported estimations of spatial orientation and the actual performance in environmental tasks [73, 76–79]. For the application in nursing home residents, the items were shortened and simplified, and the situations described were adapted to the lifestyles of the respondents.

##### Psychosocial well-being

The Satisfaction with Life Scale (SWLS) [80] is a brief instrument with five items to measure global cognitive judgements of satisfaction with one’s life on a seven-point Likert scale. A meta-analysis indicated moderate results for the internal reliability of SWLS (Cronbach’s alpha = .78) [81].

#### Secondary outcomes

The following secondary outcomes will be evaluated to further assess the efficacy of the intervention programs (see Fig. 1):

##### Physical functioning

The Short Physical Performance Battery (SPPB) [82] is a standardized instrument to measure the functionality of the lower extremities (balance, gait speed, leg strength). The test battery contains three tasks: first, the participants are asked to stand upright in three different standing positions (Romberg stance, semi-tandem stance, tandem stance) for maximum 10 s each. Afterwards they complete a 4 meter walk in comfortable gait speed, the time required is measured. After that, participants are instructed to stand up and sit down for five times and as fast as possible. The score ranges for each of these tasks between zero and four points; SPPB overall scores range from zero (low mobility) to twelve (full mobility). Improvements have been demonstrated to be clinically relevant from 0.99 points for the SPPB [82]. A hydraulic hand dynamometer (JAMAR) measures hand grip strength. Two trials with each hand will be executed. The highest value of the two trials will be used for analysis.

##### Cognitive functioning

The Montreal Cognitive Assessment (MoCA) [83] is a one-page 30-items test developed for screening of mild cognitive impairment. It includes items to assess a range of cognitive domains including executive functions, visuospatial abilities, language, attention, working memory, abstraction, and orientation to time and place. The internal reliability of the MoCA is good (Cronbach’s alpha = 0.84) [84].

##### Psychosocial well-being

The Depression in Age Scale was validated for people with and without cognitive impairment living in residential care [85]. With internal reliability above 0.821 (Cronbach’s alpha), it is a reliable measure [86]. It consists of ten items.

The eight-item Spatial Anxiety Scale reliably assesses activity-related anxiety (Cronbach’s alpha = .80) [27, 87]. The short form of the Falls Efficacy Scale-International (Short-FES-I) is a reliable (Cronbach’s alpha = .89) [88] seven-item questionnaire with a scoring range between one and four. The scores of all items are summed resulting in a total score range from seven to 28, with a higher score indicating greater concern about the possibility of falling [89].

### Interventions

To develop and verify the effect of tailored interventions as well as to meet the criteria of German health insurances [90], several steps are necessary:
Analyzing daily mobility behavior of the nursing home residentsExamining the facilities and relevant landmarksCapturing the wishes and needs for training interventions and activities of the participants as well as barriers for mobility in the specific settingsIdentifying landmarks and structural elements for daily living in the facilitiesIntegrating a)-d) into the interventionsConducting a training curriculum for future trainers in elderly care to gain sustainabilityVerifying the effects on cognitive abilities (especially spatial orientation), physical functioning and psychosocial well-being.

The exercise programs consist of 24 sessions of 45–60 min, conducted twice per week over a period of twelve weeks in groups of up to 15 participants. Exercise sessions will be administered by at least one certified exercise scientist or physiotherapist. The program follows the International Association of Gerontology and Geriatrics (IAGG) guidelines and combines previously published exercises that have proven to be beneficial for cognitive-motor performance in older people in the community and need of care [91, 92].

Based on the previous PROCARE intervention [93], three different programs will be conducted (see Table 2):

**Table 2 Tab2:** Description of the intervention (modified according to Cordes and colleagues [93])

Program	Session 1–4	Session 5–8	Session 9–12	Session 13–16	Session 17–20	Session 21–24
